## Measures

### Primary outcome measures

The primary outcome measures will include tests of single- and dual-task cognitive, gait, and postural performance in a laboratory environment, including simulated realistic conditions. The outcome measures of interest will include cognitive accuracy and reaction times, temporal gait characteristics, posturography variables, and dual-task cost scores. The older hearing aid users will be required to wear their hearing aids during all testing procedures. Two sets of research assistants will be present at each testing site—one to work with the participant and provide instructions for the tasks, and the other to work with the technical apparatus and ensure that the data are being captured and recorded appropriately.

### PERFORM Protocol at Concordia University in Montréal

*Auditory 2-Back Task.* An auditory 2-back task [41] will be used to measure working memory performance under single- and dual-task conditions. Randomly ordered single digits will be presented at a rate of every two seconds, with each trial lasting 30 s. Single digits (1–10, excluding 7) will be presented through two loudspeakers (Logitech Z623 2.1), at ear-level in height, at a 45-degree angle relative to the listener. Using two hand-held USB response buttons (Black Box ToolKit hand-held USB response button), participants will make a button response to indicate whether the number they are currently hearing is the same or different than the number presented *n* steps previously. Response buttons will be held in both hands, with each connected to a USB response box with a 2-m cable to allow for natural arm swing while walking. Participants will first complete an auditory 1-back task (i.e., indicate whether the number is the same or different than the number presented 1 step previously) in order to individually adjust the volume of the speakers. The decibel level will be continuously reduced until the participant is unable to attain 100 percent accuracy on the 1-back task or until they indicate that listening becomes effortful (i.e., will be asked if they needed to strain in order to understand the digits). Participants will first complete this task while standing and then while walking to ensure audibility with the added background noise of the treadmill. The amplitude of the stimuli will be set for the duration of the experiment at the decibel level from the walking trial where the participant achieved 100 percent accuracy and did not report that listening was effortful. During the 2-back task, participants will use the response buttons to indicate if the number is the same or different than the number presented 2 steps previously. Accuracy and reaction times will be measured. During the single-task 2-back condition, participants will complete the 2-back task while standing, with their feet on the sides of the treadmill. Participants will be required to hold the response buttons during the entire duration of the experiment in order to control for hand positioning but will be allowed to rest their arms on the treadmill railings during single-task 2-back conditions in order to provide postural support.

*Walking Task.* Participants will be required to walk on a treadmill at a self-selected speed at zero percent incline. Specifically, the speed of the treadmill will be gradually increased until the preferred speed is chosen and there are no signs of the participant sweating or being out of breath. The speed of the treadmill will be set at this speed for the duration of the experiment (i.e., will be the same speed across both single-task and dual-task conditions). During single-task conditions, participants must walk on the treadmill at their self-selected speed. During dual-task conditions, participants will simultaneously complete the 2-back task while walking. In order to measure the temporal characteristics of gait (i.e., mean and variability of step time, stride time), two electronic pressure sensors (TeleMyo Direct Transmission System) will be taped to the toe and heel of each shoe sole. Note that the treadmill will be running at the selected speed throughout the entire experiment in order to equate the same level of background noise (i.e., 50 dB SPL) across all trials.

There will be three different trial types (i.e., single-task walking, single-task 2-back, dual-task) and the experiment will follow an ABC-CBA sequence, which will occur two times, for a total of 12 trials. Dual-task costs (DTC; %) will be calculated for each of the walking and 2-back tasks: [(single-task – dual-task) / single task * 100]. DTC change scores will be calculated by subtracting the post-training DTCs from the pre-training DTCs.

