### Data analysis

#### Planned analyses

All data analyses will be completed using IBM SPSS Statistical Software and/or R. Data will be screened and corrected for normality, outliers, and missing values. Descriptive statistics (e.g., means and standard deviations for continuous variables; frequencies and percentages for categorical variables) will be presented for the demographic and baseline characteristics. Chi square tests (for categorical variables) or One-Way ANOVAs (for continuous variables) will be used to determine if there are any differences between groups at baseline (i.e., middle-aged vs. older adults vs hearing aid users; training vs. control groups).

In order to evaluate our primary hypothesis (i.e., that executive function training will lead to greater improvements in dual-task performance compared to a wait-list control group), separate 3 × 2 × 2 Mixed Factorial ANOVAs will be conducted for each of the primary outcome measures (i.e., 2-back accuracy and reaction times, CRM accuracy, temporal gait parameters, posturography variables, DTC scores), whereby the Between-Subjects factors will include Age/Hearing Group (middle-aged, older adult, hearing aid users) and Training Group (cognitive training, control), the Within-Subject factor will include Time (pre- vs. post-evaluations), and Covariates will include sex and education. Observation of a statistically significant Time by Training Group interaction in any of the primary outcome measures will be considered preliminary evidence for training efficacy. In order to examine our second and third hypotheses (i.e., that largest improvements in dual-task performance and greatest augmentation of brain activity will be found in older hearing aid users, followed by normally-hearing older adults, and then middle-aged adults) separate One-Way ANOVAs will be used on the dual-task and HbO change scores within the cognitive training group, whereby the Between Subjects factor will include Age/Hearing Group (middle-aged, older adult, hearing aid users). Observation of a statistically significant main effect of Group will be followed up by post hoc pairwise analyses with Bonferroni corrections in order to determine whether our hypotheses are supported.

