Linear mixed effects models will also be fitted for each of our outcome measures, particularly if there is a large amount of missing data or if there is an unequal amount of variance across groups. Specifically, Fixed effects will include Age/Hearing Group (middle-aged, older adult, hearing aid users), Training Group (executive function training, control), Sex (male/female), and Time (Pre- vs. Post-Training), Random effects will include the individual participants, and Covariates will include education.

Lastly, in order to elucidate whether brain activity reflects neural compensation or inefficiency, correlations between dual-task performance and HbO levels will be conducted at baseline and after 12 weeks. All statistical tests will be two-tailed, and a *p*-value of less than 0.05 will be considered to indicate statistical significance. Effect sizes will be calculated using Hedges’ *g.*

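### At a fixed belt speed, mean step and stride time have no stated favourable direction, yet a significant change either way could count as evidence of efficacy

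*Protocol article*

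**What the plan says.** Protocol article, PERFORM Protocol at Concordia University in Montréal, Walking Task: participants choose a comfortable treadmill speed. Then "The speed of the treadmill will be set at this speed for the duration of the experiment", which the article explains as meaning that it "will be the same speed across both single-task and dual-task conditions". The gait outcomes are the "temporal characteristics of gait (i.e., mean and variability of step time, stride time". The dual-task cost (DTC) is the signed percentage (single − dual) / single × 100, with one formula for walking and for the 2-back, and the DTC change score is pre-training minus post-training.

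Primary outcome measures: the outcomes of interest include "temporal gait characteristics, posturography variables, and dual-task cost scores".

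Planned analyses: each primary outcome gets its own ANOVA, the list being "2-back accuracy and reaction times, CRM accuracy, temporal gait parameters, posturography variables, DTC scores". An "interaction in any of the primary outcome measures will be considered preliminary evidence for training efficacy". The last paragraph adds that "All statistical tests will be two-tailed", at the 0.05 level.

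No section says whether a longer or a shorter mean step or stride time is better. The only remark bearing on direction for gait is in the Discussion, and it concerns variability, not the means.

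**The concern.** On a belt that sets the speed, a person who stays in place cannot walk faster or slower. What remains free is how that speed is made up: fewer long steps or more short ones. Mean step time and mean stride time record that choice. Nothing in the article makes either choice an improvement in dual-task walking.

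The efficacy rule nevertheless covers these means and their costs, uses two-tailed tests, accepts any one significant measure, and does not require the difference to be favourable. A shift in stepping pattern in the trained arm, in whichever direction, would meet the rule as written. The hypothesis being tested is greater improvement in dual-task performance, and an outcome without a direction cannot test improvement.

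**Working it through.** The plan gives no figure of its own on this point, so there is none to reproduce. Belt speeds, step times and effect sizes below are assumptions for illustration.

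**1. Identity within a session.** Mean step length = belt speed × mean step time; the same holds for strides.
- Assumed 1.0 m/s, step time 3% longer: 0.550 → 0.5665 s. Step length goes 0.550 → 0.5665 m and cadence 60/0.550 = 109.1 → 60/0.5665 = 105.9 steps/min. Speed is unchanged.
- Assumed speeds of 0.8 to 1.2 m/s with step times of 0.50 to 0.60 s give the same pattern: 3% more time is exactly 3% more length.
- Assumed 1.1 m/s, stride time 1.10 → 1.05 s: stride length 1.1 × 1.10 = 1.210 m → 1.1 × 1.05 = 1.155 m, which is 5.5 cm shorter at the same speed.

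**2. The signed cost supplies no direction.**
- Single 0.55 s, dual 0.57 s: (0.55 − 0.57)/0.55 × 100 = −3.64%.
- Single 0.55 s, dual 0.53 s: (0.55 − 0.53)/0.55 × 100 = +3.64%.

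The article does not say which of these is a cost. Now let each of these two people halve the shift after training, to dual-task times of 0.56 s and 0.54 s, so that the costs become −1.82% and +1.82%. The change score (pre − post) is −3.64 − (−1.82) = −1.82 for the first and 3.64 − 1.82 = +1.82 for the second. The same move toward zero gets opposite signs, and the two average to nothing. On absolute values both score 3.64 − 1.82 = +1.82.

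**3. Step and stride means are nearly one outcome.** A stride is two steps, so mean stride time is about twice mean step time. With 1.10 s single and 1.14 s dual, the stride cost is (1.10 − 1.14)/1.10 × 100 = −3.64%, the same as the step cost.

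**4. The rule treats both directions alike.** The Design section gives 60 participants per site, or about 30 per arm. After the 10% attrition in the Sample size section this is 60 × 0.9 / 2 = 27 per arm. For a two-arm comparison of change (t test, 2n − 2 degrees of freedom, noncentrality d × √(n/2), two-sided 0.05, ignoring the age/hearing factor and covariates), the probability of a significant result in the direction of the true difference is:

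| Assumed d | 30 per arm | 27 per arm |
|---|---|---|
| 0.3 | 0.207 | 0.190 |
| 0.5 | 0.478 | 0.438 |
| 0.8 | 0.861 | 0.822 |

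Each value is the same whether the trained arm's times lengthen or shorten.

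**5. Before versus after training.** The wording on a constant speed is explained by reference to single- and dual-task conditions; it does not clearly say that the pre-training speed is used again 12 weeks later. If speed is chosen again and rises from an assumed 1.00 to 1.13 m/s (the 0.13 m/s gain that the Sample size section cites from an earlier trial), a person with an unchanged 0.55 m step goes from 0.55/1.00 = 0.550 s to 0.55/1.13 = 0.487 s. The raw mean then also carries the change in chosen speed.

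**The case against.** The strongest reply has five parts.

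- **The identity is secure only within a session.** The efficacy test is a pre/post contrast. A reader might infer that mean stride time can change over the trial only through stride length. The article does not support that, because it does not settle whether the speed is carried over. This part stands. It changes the description of the raw means but gives them no direction.
- **A direction can be supplied.** A reader might infer that no correct sign exists and that no repair is possible. That goes too far. At matched speed, a dual-task shift away from the person's own single-task timing can be read as interference whichever way it goes, so a cost nearer zero is interpretable. The ambiguity lies in the raw means and in the signed cost that the article defines.
- **Variability is not a clean alternative.** The Discussion cites lower gait variability together with poorer word recognition as an example of putting posture ahead of cognition. Lower variability alone can therefore mark a trade-off. This stands and shapes the fix.
- **The claim is modest and framed by a directional hypothesis.** The article speaks of preliminary evidence for training efficacy, not of improved mobility, and two-tailed testing does not mean that the investigators would present a worsening as a benefit. This is fair. But for these means the article does not say what a worsening would be.
- **A full protocol or analysis plan may state the direction.** It may. The article itself, however, fixes the constant speed, the outcomes, the two-tailed tests and the any-measure rule, and it is that combination which allows a change either way to count.

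**Conclusion.** The point holds for mean step time, mean stride time and their signed dual-task costs at the Concordia site. Within a session these can differ between conditions only through a trade between step length and cadence. If the belt speed is chosen again after training, the raw means move with speed as well. They have no stated favourable direction, and the efficacy rule would accept a significant interaction either way.

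The extent is limited. A reader might count the means as a third of the Concordia measures (two of six, or six of 18 once single-task, dual-task and cost scores are multiplied out). The article gives no such count, and the two means are close to a single quantity, so the figure overstates the exposure. The variability measures and the 2-back outcomes are not affected. The probabilities in the table rest on assumed effect sizes; they show symmetry, not how likely a spurious finding is.

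This does not undermine the trial. It is a cheap improvement that lets the gait results bear on the stated hypothesis.

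**What to change.** In the Walking Task text and in Planned analyses:

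1. Report mean step time, mean stride time and their signed dual-task costs descriptively. If a cost for these means is kept as an efficacy outcome, use its absolute size, with movement toward zero defined as improvement.
2. Keep step-time and stride-time variability as the Concordia gait outcomes, with lower pre-specified as better, and interpret them alongside 2-back accuracy and reaction time so that a trade-off is visible.
3. Count a Time by Training Group interaction as evidence of efficacy only when it lies in the pre-specified favourable direction. Tests can stay two-tailed.
4. State whether the pre-training belt speed is reused at the post-training session or chosen again.

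Cost: no new data, visits or staff. There are fewer outcomes able to support efficacy, and because these are listed primary outcomes of a registered trial that is still recruiting, the change is an amendment and not merely a matter of wording.

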Overall, there will be a total of six trial types: 1) single-task 2-back eyes open, 2) single-task 2-back eyes closed, 3) single-task standing eyes open, 4) single-task standing eyes closed, 5) dual-task eyes open, 6) dual-task eyes closed. Participants will complete all trial types in an ABC-CBA sequence with the three different conditions (A: single-task standing, B: single-task 2-back, and C: dual-task). This will occur two times, once for the eyes open condition, and once for the eyes closed condition. The order of trials (i.e., eyes open vs. eyes closed) will be counter-balanced across participants. DTCs (percentage) will be calculated for both the standing and 2-back tasks: [(single-task – dual-task) / single task * 100]. DTC change scores will be calculated by subtracting the post-training DTCs from the pre-training DTCs.

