In order to manipulate attentional load and listening difficulty, we will include a block of trials in which the location of the target word will be certain 100% of the time (i.e., participants will be told the target word will always be presented at 0 degrees; termed 100% trials; lower cognitive load) and a block of trials in which the location of the target word will be uncertain, presented from the centre 60% of the time and from the left 40% of the time (i.e., participants will be told that the target word will be coming from the middle 60% of the time and from the left 40% of the time; termed 60% trials; higher cognitive load). Participants will complete these 100% and 60% trial types in single and dual-task conditions.

*Postural Task*. Static balance will be measured on a force platform in a semi-tandem stance, with one foot slightly in front of the other. Postural measures will include spatial (centre of pressure path length; cm), temporal (velocity; cm/s) and variability (root means square, standard deviation) measures in the anterior–posterior (front and back) and medial–lateral (side-to-side) orientations.

Overall, there will be a total of 5 different trial types: 1) single-task CRM (100%/low cognitive load), 2) single-task semi-tandem standing, 3) dual-task (60%/high cognitive load), 4) single-task CRM (60%/high cognitive load), 5) dual-task (100%/low cognitive load). Participants will complete all trial types in this order and will then repeat the trials in the reverse order, for a total of 10 trials. DTCs (percentage) will be calculated for both the standing and CRM tasks: [(single-task – dual-task) / single task * 100]. DTC change scores will be calculated by subtracting the post-training DTCs from the pre-training DTCs.

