The dual-task module aims to improve divided attention. Participants will complete a visual discrimination task whereby they will need to make a response to one type of image (single-task; i.e., modes of transportation or fruits;) or two types of images concurrently (dual-task; i.e., one image reflecting a mode of transportation and another image of a fruit). Participants will complete pure blocks of only single-task trials (single-pure trials) or only dual-task trials (dual-pure trials) or will complete mixed blocks that randomly involve one (single-mixed trials) or both tasks (dual-mixed trials). For the dual-task trials, participants will be instructed to respond to both stimuli equally. However, as the training progresses, participants will need to prioritize one hand over the other to increase the level of difficulty (i.e., in the dual-task trials when two images are presented, participants will be asked to make a response using their left or right hand first before making a response with the other hand).

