Another strength of the study protocol is the use of ecologically valid measurement techniques, including subjective and objective measures of hearing, cognition, and mobility, as well as an immersive, multisensory VR environment to assess realistic sensory-cognitive-motor challenges. Our previous research assessing dual-task performance in a simulated street crossing environment showed that older adults tended to prioritize posture over cognitive performance (e.g., reduced gait variability at the cost of word recognition accuracy) [19, 28]. As such, our study will add to this growing literature and extend previous research using traditional laboratory-based experiments.

A final strength of the protocol is the use of portable fNIRS to examine brain activity in the prefrontal cortex during dual-task walking before and after training. Currently, there are inconsistent findings with regard to the effect of dual-tasking on brain activity across younger and older adults, with some researchers showing a bilateral upregulation in the prefrontal cortex in older adults compared to younger adults [79, 80], others showing comparable brain activity [81], and others showing greater activity in younger adults compared to older adults [82]. It also remains unclear how brain activity during dual-tasking changes following cognitive training. Scaffolding theories propose that training may increase compensatory mechanisms in response to declining brain structure with age via an up-regulation of frontal brain regions [83]. However, the effect of cognitive training on brain activity during dual-tasking in older adults with hearing loss has yet to be examined. We therefore hope that our study will elucidate some of these inconsistencies and contribute to the growing knowledge on mobile brain imaging.

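### The efficacy rule judges each dual-task cost on its own, so a shift of priority between the motor and the cognitive task could be labelled efficacy

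*Protocol article*

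**What the plan says.** All three paradigms compute one cost per task from the same dual-task trials.

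- Walking with 2-back (PERFORM Protocol): "Dual-task costs (DTC; %) will be calculated for each of the walking and 2-back tasks".
- Standing with 2-back (Auditory 2-back paradigm): "DTCs (percentage) will be calculated for both the standing and 2-back tasks".
- Standing with CRM (CRM Paradigm): "DTCs (percentage) will be calculated for both the standing and CRM tasks".

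The formula is the same throughout, "single-task – dual-task) / single task * 100", whichever measure goes into it. For change, "DTC change scores will be calculated by subtracting the post-training DTCs from the pre-training DTCs".

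Planned analyses then runs a separate mixed ANOVA for each primary measure, including the dual-task costs. A significant Time by Training Group interaction in any of them "will be considered preliminary evidence for training efficacy". All tests are two-tailed at 0.05, and the mixed models are also fitted outcome by outcome. The hypothesis that opens the paragraph is directional: greater improvement in dual-task performance than in the wait-list group.

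The article expects trade-offs in this field. The Background section on effortful listening says that older adults with hearing loss tend to protect posture or walking over cognition. The Discussion says of the group's earlier work that "older adults tended to prioritize posture over cognitive performance (e.g., reduced gait variability at the cost of word recognition accuracy".

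**The concern.** The motor and the cognitive score from one trial compete for the same attention; that is the theory behind the study. A better score in one task is therefore ambiguous until the other is known. It may be a real gain, or attention taken from the paired task. The article reads paired scores this way when it discusses earlier results, but its own success rule does not.

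Randomisation does not settle the question. If training changes how participants divide attention, that change appears as the Time by Training Group interaction. Nor is this a multiplicity problem. A change of priority is a true effect on each of the two scores, so a stricter alpha makes it harder to detect but does not alter what a detected effect means.

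At stake is the meaning of the primary claim: whether training improved dual-task performance or changed which task participants favour.

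**Working it through.** The plan gives no figure for this point. The sample size of 18 per group is not in question here.

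**1. Is the paired score considered anywhere?** The three cost definitions, the ANOVA paragraph, the efficacy sentence, the change-score ANOVAs for the second and third hypotheses, and the mixed models all work one measure at a time. The article describes no joint analysis of paired costs and no condition linking them.

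**2. Does the formula fix a direction?** Cost = (single − dual) / single × 100. Illustrative values:

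- Accuracy worsens from 90 to 80: (90 − 80) / 90 × 100 = +11.1%.
- Reaction time worsens from 800 to 900 ms: (800 − 900) / 800 × 100 = −12.5%.

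Now let training halve both decrements (dual-task accuracy 85, reaction time 850 ms). The post-training costs are +5.6% and −6.25%. Change is pre minus post:

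- Accuracy: 11.1 − 5.6 = about +5.6 points (90, 80 and 85 give 5.56 exactly to two decimals).
- Reaction time: −12.5 − (−6.25) = −6.25 points.

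The same kind of improvement is positive for one measure and negative for the other. Gait variability and sway, where larger values are worse, behave like reaction time.

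**3. What a trade-off looks like.** Assumed figures, costs oriented so that higher is worse: motor cost falls from 10% to 4%, and 2-back cost rises from 20% to 26%. The mean is (10 + 20)/2 = 15% before and (4 + 26)/2 = 15% after. The motor interaction, 6 points better, could be cited as efficacy. The figures were chosen to cancel and are illustrative only.

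**4. How often could the rule be met?** Inputs from the article: 60 per site (Design) in equal arms (Randomization), so 30 per arm; with 10% attrition (Sample size), 30 × 0.9 = 27. Assumed: one motor and one cognitive cost; training shifts them by +s and −s SD (net zero in equally weighted SD units); correlation of changes −0.5, 0 or 0.5. Each score was tested with a two-sided t-test on change at 0.05, which equals the Time by Training Group test without covariates or the age/hearing factor. There were 20,000 simulated trials per setting. The table gives the percentage of trials declaring efficacy; ranges cover both arm sizes and all three correlations.

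| Rule | s = 0.3 | s = 0.5 | s = 0.8 |
|---|---|---|---|
| Any significant interaction, either direction | 29.9–40.5 | 60.3–80.4 | 92.9–99.8 |
| Any significant improvement | 18.6–20.8 | 43.5–47.8 | 81.8–86.5 |
| Improvement, paired cost not significantly worse | 10.9–19.6 | 16.5–32.6 | 9.0–17.1 |

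A mean of the two standardised, sign-aligned costs, tested for improvement, declares efficacy in 2.3–2.7% in every setting. Requiring that the paired estimate is not worse at all gives 0–6.1%.

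**The case against.** Several counter-arguments have force.

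- **Direction is implied.** The efficacy sentence serves a hypothesis of greater improvement, and two-tailed testing of a directional hypothesis is standard. A reader might infer that a worsening interaction would count as success. That requires detaching one sentence from its paragraph, so the relevant row of the table is the second. What stands is that the formula does not align signs.
- **The second task is not ignored.** Both costs are primary measures with their own analyses, so opposite movement would be visible in the results. The gap is in the rule for the claim, not in what is measured.
- **No figure shows that training causes a shift.** The only training effects on dual-task costs cited under Sample size (g = −0.83 for n-back, g = −0.11 for walking speed) are both described as gains. They show that a claim may rest on the cognitive side alone, not that the motor side worsens.
- **The training link is thin.** A reader might infer that the programme teaches trade-offs because in its dual-task module "participants will need to prioritize one hand over the other to increase the level of difficulty". That passage concerns which hand answers first to two images on a screen. It involves no gait or balance and does not support the inference.
- **Zero net gain depends on weighting.** The Background describes favouring posture as a way to keep mobility safe. Nothing in the article justifies weighting the two tasks equally.
- **The label is only preliminary evidence.** True, but it is the only criterion stated for the primary hypothesis, and the stated objective is to establish efficacy.

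None of these supplies the missing condition on the paired cost.

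**Conclusion.** The point holds in a limited form. As written, one significant interaction on one side of a dual-task pair is enough for a claim of preliminary efficacy, whatever happened on the other side. A shift of priority could therefore be labelled efficacy. The documents do not show that it would be, because the size and direction of any shift are unknown.

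If a pure shift of 0.3 to 0.8 SD occurred, a rule requiring improvement would be met in roughly 19% to 87% of trials. This rests on the assumed shifts and correlations, on two measures only, and on equal weighting of the tasks.

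A reader might also infer that the whole trial accepts poorer balance as success in people at risk of falls. The article does not support that: it ties falls risk to hearing loss, two of the three groups have normal hearing, and poor scorers on the Mini-BESTest are excluded.

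**What to change.** Amend Planned analyses as follows.

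1. Orient every dual-task cost so that higher means worse, and count an interaction as evidence of efficacy only when it favours training.
2. For each paradigm (walking/2-back, standing/2-back, standing/CRM), present the motor and cognitive cost effects side by side with confidence intervals. Describe the result as improved dual-task performance only when the paired cost shows no evidence of worsening.
3. Report opposite movement as a change in prioritisation, not as efficacy.

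Any combined cost should be supportive only. It should use one pre-named motor and one pre-named cognitive measure, standardised before averaging; otherwise the more variable percentage dominates, and the choice among many gait, sway and cognitive measures stays open.

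This needs no new data or visits. The cost is a more cautious label for some single-domain gains. The condition in item 2 is a compromise. Judged by significance alone, it would still pass 9–33% of the simulated pure trade-offs, so the paired interval must always be shown. Requiring a paired point estimate that is not worse would be too strict: with no true effect on the paired task, a genuine gain in the other would fail about half the time (symmetric, independent estimates assumed).
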